## Abstract

**Background:**

Due to climate change, the population and health care systems face an increasing burden of weather-related health risks. Emergency departments (EDs) are one of the first points of contact for acute and emergency care and insights into population health. Previous research has demonstrated that climate change-based weather phenomena have an impact on ED usage and morbidity. However, research shows inconsistent results for some weather phenomena and disease groups, and no corresponding evidence is yet available for Germany.

**Objective:**

This study aims to investigate the association between climate-related weather conditions and ED usage and morbidity in Germany. It focuses on identifying particularly vulnerable patient groups, developing indicators for syndromic surveillance, and testing prediction models to support clinical and public health decision-making.

**Methods:**

KlimaNot is a multicenter, registry-based observational cohort study with retrospective and prospective components. The primary analysis is a prespecified retrospective evaluation using routinely collected encounter data from the German National Emergency Department Data Registry (AKTIN), comprising approximately 6.35 million ED visits from up to 56 EDs (2019-2024). Hospital-level environmental exposures (eg, temperature and selected air pollutants) will be linked to each participating ED based on location and summarized to daily metrics. The primary endpoint is daily all-cause ED visit volume at the hospital-day level. Secondary endpoints include hospital admission probability, syndromic and diagnostic case-mix, referral source and mode of transport, and routinely recorded proxies of clinical severity (eg, triage acuity). Heat effects will be quantified using models allowing for nonlinear exposure–response relationships and delayed (lagged) effects, with adjustment for site, seasonality and time trends, weekday, and public holidays; effect modification by age, sex, multimorbidity proxies, and area-level socioeconomic deprivation will be assessed. Additional analyses include a predefined case study for the region Stuttgart, leveraging extended longitudinal and more detailed pathway data, development and validation of heat-sensitive syndromic surveillance indicators, evaluation of short-term forecasting models of ED usage, and an ancillary prospective geriatric substudy collecting patient-reported and functional outcomes to better characterize vulnerability in the oldest-old.

**Results:**

Retrospective data analyses are ongoing and scheduled for completion by April 1, 2026. The prospective study will expect results by September 1, 2026.

**Conclusions:**

This study will provide the first robust evidence on the impact of climate change–related weather conditions on ED usage and morbidity in Germany. The findings aim to support early detection, preparedness, and targeted protection strategies for vulnerable populations and inform clinical and public health decision-making.

**Trial Registration:**

German Clinical Trials Registry DRKS00033214; https://drks.de/search/en/trial/DRKS00033214 and German Clinical Trials Registry DRKS00037822; https://drks.de/search/en/trial/DRKS00037822

**International Registered Report Identifier (IRRID):**

RR1-10.2196/82267

## Introduction

### Background

As a result of climate change, there is an expansion of weather-related health risks affecting the population and challenging health system actors. Heat waves can lead to increased mortality [1,2]. The unusually high summer temperatures in Germany between 2018 and 2020 resulted in a significant number of deaths, with approximately 8700 heat-related deaths in 2018, 6900 in 2019, and 3700 in 2020 [2]. Regarding morbidity, it is already known that individuals afflicted with respiratory disorders, including chronic obstructive pulmonary disease and asthma, are susceptible to the adverse effects of high temperatures [3]. This susceptibility is further exacerbated by environmental pollutants that heighten sensitivity to inflammatory reactions [4,5]. Cardiovascular diseases such as myocardial infarction and decompensating heart failure [6-8], as well as acute kidney injury resulting from dehydration, are associated with high temperatures [9,10]. Furthermore, natural disasters and extreme weather events have been associated with psychological distress, cognitive impairment, and headaches [11,12].

Patients with multiple comorbidities, older people, children, and adolescents are particularly vulnerable during extreme heat [13-15]. Masselot et al [16] examined the impact of extreme temperatures on different age groups in 854 European cities. Their findings emphasize that heat-related health risks increase with age. Specifically, older adults (65 years and older) are more vulnerable to extreme temperatures, experiencing higher relative risks of mortality compared to younger adults. In the United States, it has been shown that extreme heat results in a higher occurrence of emergency department (ED) visits due to heat-related illness, kidney diseases, and mental disorders among both younger and older adults [17]. Bernstein et al [15] demonstrated that extreme heat during the warm season has led to a significant increase in ED visits at children’s hospitals in the United States. The analysis revealed that high temperatures are associated with a 17% increased risk of all-cause emergency visits. The associations were particularly pronounced for heat-related illnesses such as dehydration and electrolyte disorders (83% increased risk), bacterial enteritis (35% increased risk), and ear infections (30% increased risk). Children with comorbidities, genetic susceptibilities, or those who face adverse social determinants of health are particularly at risk [15]. Thus, the question of how climate change-related weather influences the emergency and acute medical care needs of different socioeconomic groups becomes increasingly important for health care research.

Although there is already extensive evidence on the impact of weather and the environment on population health, the influence of weather-related factors on the use of EDs is still not sufficiently understood**.** While there is unambiguous evidence of a positive association between high ambient temperatures and ED visits due to directly heat-sensitive diseases such as dehydration and electrolyte imbalances, there is inconclusive evidence on the relationship between temperature and cardiovascular, renal, and respiratory diseases [18-20]. EDs serve as a central element of the German health care system and provide crucial insights into current emergency and acute medical care trends. Given the ubiquitous effects of global climate change and the existing evidence, we hypothesize that climate-change-related weather conditions, such as extreme heat days, significantly influence population health and the usage of EDs in Germany. Moreover, we assume geographical differences and a group-specific impact on children, older, and patients with multiple comorbidities.

### Objectives

We will link routine ED encounter data from the German National Emergency Department Data Registry (AKTIN Registry) with high-resolution environmental data to investigate heat-related impacts on acute and emergency care in Germany. The study follows a hierarchical objective structure with a prespecified primary retrospective analysis, secondary clinical objectives, and additional exploratory components (syndromic surveillance and prediction modeling).

### Primary Objective (Prespecified Retrospective Analysis)

Objective 1 (O1): the primary objective is to quantify the association between ambient heat and acute-care demand in Germany, using a prespecified retrospective analysis of daily ED visit volumes as primary outcomes. We will compare heat days with comfort days, quantify exposure–response relationships, and characterize immediate and delayed effects of heat over predefined lag windows as the primary objective. In addition, we will identify temperature thresholds at which ED attendances and hospital admission probabilities increase and assess whether these associations differ across vulnerable patient groups, with a focus on children, older, and people with multiple comorbidities.

### Secondary Clinical Objectives (Retrospective; Secondary Endpoints)

Objective 2 (O2): we will analyze hospital admission rates related to heat exposure.

Objective 3 (O3): we will examine shifts in syndromic and diagnostic patterns on heat days.

Objective 4 (O4): we will assess pathways to emergency care, including referral source and mode of transport, by applying suitable models for compositional or proportion outcomes.

Objective 5 (O5): we will assess clinical severity at ED presentation using routinely recorded proxies, including triage acuity and high-acuity presentation rate.

### Ancillary Prospective Geriatric Substudy

Objective 6 (O6) (ancillary prospective substudy; separately registered): we will characterize patient-reported heat-related symptoms and functional impact in oldest-old patients (aged 85 years or older) to better describe vulnerability beyond routine registry variables.

### Exploratory Objectives (Hypothesis-Generating and Methodological Components)

Objective 7 (O7): we will assess the suitability of routine ED data for continuous syndromic surveillance of weather-sensitive morbidity. The initial focus is on the development of an indicator monitoring population health during heat events, which has been established in other EU countries for several years [21,22].

Objective 8 (O8): we will further develop and evaluate short-term prediction models of ED usage under varying weather constellations to support operational preparedness and public health decision-making.

Across objectives O1-O5, we will examine differences across vulnerable patient groups and assess regional and socioeconomic disparities using area-level indicators and urban-rural context as potential effect modifiers. A predefined Stuttgart case study will be used for selected secondary analyses that benefit from extended longitudinal coverage and additional pathway detail (eg, basin-valley contrasts).

## Methods

### Study Design and Setting

KlimaNot is a multicenter, registry-based observational cohort study that links routinely collected ED data with hospital-level environmental exposures and comprises both retrospective and prospective components. The retrospective component includes multicenter analyses of ED usage and morbidity as well as the development of syndromic surveillance indicators and prediction models based on linked routine data from participating EDs across Germany. To characterize the structural context of the participating EDs and to assess potential selection effects, key hospital- and location-related characteristics were extracted, including hospital type [23,24], level of emergency care, municipality population size, urban or rural location [25], and total hospital bed size [26] (Table 1).

**Table 1 table1:** Characteristics of participating AKTIN^a^ – EDs^b^ (N=56).

Characteristics		EDs, n (%)
**Hospital type**		
	Community or other hospital	34 (60.7)
	University hospital	22 (39.3)
**Hospital bed capacity**		
	<100	0 (0)
	100-199	3 (5.4)
	200-499	9 (16.1)
	≥500	44 (78.6)
**Emergency care level**		
	Basic	7 (12.5)
	Specialized	9 (16.1)
	Maximum	40 (71.4)
**City population**		
	<100,000	17 (30.4)
	100,000-250,000	17 (30.4)
	250,000-500,000	8 (14.3)
	>500,000	14 (25)
**Location type^a^**		
	Urban	41 (73.2)
	Rural	15 (26.8)

^a^AKTIN: German National Emergency Department Data Registry.

^b^ED: emergency department.

In addition, an ancillary prospective substudy in geriatric clinics collects patient-reported and functional outcomes in the oldest-old population to complement routine registry data. The retrospective and ancillary prospective components are registered separately in German Clinical Trials Registers (DRKS). This protocol prespecifies the main endpoints and analytical framework for the overall study program, while detailed procedures and additional endpoints of the ancillary prospective substudy are specified in its corresponding DRKS record and will be reported separately.

### Data Sources

#### Overview

The study will draw on 4 data sources: routinely collected ED data from the AKTIN ED Registry, additional information from a regional dataset of routine data drawn from the ED Klinikum Stuttgart, survey data from geriatric patients, and environmental exposure data provided by the German Meteorological Service (*Deutscher Wetterdienst* [DWD]) and the Federal Environment Agency (*Umweltbundesamt* [UBA]).

#### Routine ED Records

Retrospective data will be sourced from the AKTIN Registry [27]. The registry is implemented on the underlying AKTIN infrastructure, a nationwide federated data network operated within the Network University Medicine [28]. For the study, a total of 56 EDs throughout Germany, including clinics of different care levels in cities with different population sizes, provide electronic health records from all ED visits documented in the respective ED in the years 2019 to 2024.

Across participating EDs, approximately 6.35 million ED visits will be available for the study period, with an anticipated exclusion of up to 10% due to missing key variables. This retrospective ED dataset contains patient-specific information on age, sex (male, female, or other), and the zip code of the patient’s place of residence, as well as administrative data on mode of transport to the ED, time of admission, and mode of disposition (discharge to home, transfer to other hospital, inpatient admission, or death). Furthermore, it contains the following treatment information: ED diagnoses in the form of *ICD-10-GM* (*International Classification of Diseases and Related Health Problems, Tenth Revision, German Modification*) codes with a labeling of the main ED diagnosis, additional information on diagnosis certainty (secured, suspicion of, condition after or exclusion of diagnose), chief complaint in the form of Canadian Emergency Department Information System – Presenting Chief Complaints (CEDIS-PCL) codes, urgency level coded as Manchester Triage System (MTS) or Emergency Severity Index (ESI), vital parameters, Glasgow Coma Scale (GCS) and isolation status [29-31]. In case of an inpatient admission following the ED visit, inpatient treatment information according to the German social laws regulating the billing of inpatient services (§ 21 Krankenhausentgeltgesetz, KHentG) is available. This information contains the inpatient discharge diagnosis, also coded as *ICD-10-GM*. Multiple ED visits by the same person during the study period cannot be attributed due to data protection requirements.

All ED data will be sourced via established AKTIN registry processes in a standardized format and provided to the study team as a consolidated study dataset for analysis [28]. Before any analyses are conducted, we will perform systematic data quality checks, including verification of variable formats (dates, times, and *ICD-10-GM* codes), plausibility checks for key variables (eg, age range, sex, and time stamps), and identification of potential duplicate records based on site, admission date and time, and local encounter identifiers. Obvious duplicate entries and technically invalid records will be removed in accordance with predefined rules.

#### Stuttgart Regional Dataset

For the analysis of basin-valley differences in Stuttgart, additional regional information beyond the regular dataset is available for the period from 2011 to 2023. This dataset comprises approximately 409,000 cases and enables longer-term analyses. Compared to the AKTIN ED Registry, the dataset provides more detailed information on emergency patients and their treatment. In addition to diagnoses and symptoms, treatment times, duration, diagnostics, place of residence, and physician requirements are recorded. This allows for an analysis of not only the emergency presentation but also the diagnostic and therapeutic effort involved.

#### Prospective Geriatric Data Collection

Additional prospective data on the individual functional level of old patients will be collected at 3 participating study centers (Department of Geriatric Medicine Aachen, Hospital Fürth, and University Clinic for Geriatric Medicine Oldenburg). All geriatric patients admitted to the geriatric ward via the participating EDs at the 3 study centers will be screened and invited to participate in the prospective substudy. Written informed consent will be obtained during inpatient treatment by trained study personnel at the participating centers. In addition to routinely performed comprehensive geriatric assessment, the substudy will collect standardized patient-reported and functional outcomes, including the Parker Mobility Score (mobility) [32], the SF-12 Health Survey (health-related quality of life) [33], and parts of the questionnaire on social situation [34]. A project-developed questionnaire will assess self-reported heat exposure and heat-related problems in the days preceding hospital admission. A follow-up survey approximately 6 weeks after discharge will assess longer-term outcomes, such as reduced mobility and increased level of dependency (eg, discharge to a nursing home). In addition, inpatient data will be used to describe specific characteristics of the geriatric cohort using the Hospital Frailty Risk Score [35] and investigate outcomes as length of stay and in-hospital mortality. To maximize recruitment and follow-up adherence in this vulnerable cohort, only geriatric centers with established research experience are included. Study personnel will be dedicated to the substudy, experienced in geriatric care, and located directly on the wards to enable repeated opportunities for study information, support with questionnaires, and communication with relatives or legal representatives when required. Contact information for follow-up will be updated by the day of discharge, particularly in case of changes in the discharge destination (eg, nursing home). Follow-up will be conducted within a 2-week contact window around the 6-week time point, with repeated contact attempts if needed. Based on treatment capacities and prior patient volumes at the participating centers, we estimate that approximately 281 patients will meet the inclusion criteria during the planned recruitment period. Based on experience from previous geriatric studies, we expect that approximately 50% will consent to participate (approximately 139 participants). For the 6-week follow-up, a dropout rate of approximately 50% is anticipated.

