#### Informed Consent

The use of the ED data has been approved by the AKTIN Data Use and Access Committee and is subject to AKTIN’s data protection regulations. Written informed consent will be obtained from all patients participating in the ancillary prospective geriatric substudy. Both the retrospective registry-based study and the ancillary prospective geriatric substudy are registered in the DRKS and are governed by their respective approvals (AKTIN data access for retrospective analyses; site-specific ethics and informed consent for the prospective substudy).

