#### Descriptive Overall Population Analyses

The descriptive analysis of the overall population will characterize the overall cohort and support the planning of relevant subgroup analyses. It will include key aspects of the cohort based on multiple variables, including sociodemographic factors (age and gender), presenting complaints (CEDIS-PCL), initial triage assessment (MTS or ESI), patient referral pathways, hospital stay duration, discharge outcomes, diagnostic categories (*ICD-10-GM*), and socioeconomic status (GISD). Continuous variables will be summarized using mean (SDs) or median (IQRs), and categorical variables as counts and percentages. Distributions will be presented graphically (eg, histograms and density plots).

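### Substudy participants enter by consent during the hospital stay whose length and mortality are outcomes, so deaths and discharges before consent cannot be counted

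*Protocol article*

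**What the plan says.** The section Prospective Geriatric Data Collection fixes both the entry rule and the outcomes.

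- **Source population:** "All geriatric patients admitted to the geriatric ward via the participating EDs at the 3 study centers will be screened and invited to participate".
- **Entry:** "Written informed consent will be obtained during inpatient treatment by trained study personnel at the participating centers". The Informed Consent section makes this a condition for everyone: "Written informed consent will be obtained from all patients participating in the ancillary prospective geriatric substudy".
- **Numbers:** "we estimate that approximately 281 patients will meet the inclusion criteria during the planned recruitment period", and "we expect that approximately 50% will consent to participate (approximately 139 participants"). For the later survey, "For the 6-week follow-up, a dropout rate of approximately 50% is anticipated".
- **Outcomes:** inpatient data are to be used to describe the geriatric cohort and to "investigate outcomes as length of stay and in-hospital mortality".

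The statistical section on the substudy (O6) plans regressions of substudy outcomes on heat exposure measures. Its sensitivity analyses are for missing data and loss to follow-up. Under Strength and Limitations, the one limitation given for the geriatric survey is that it is not powered and is exploratory.

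**The concern.** Cohort entry falls inside the interval over which both outcomes are measured. Every participant has, by construction, survived and stayed in hospital from admission to consent. Deaths in that interval drop out of the mortality numerator and stays that end in it drop out of the length-of-stay distribution. This is left truncation, with an immortal interval before consent.

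What is at stake is the reading of two descriptive figures. The substudy is meant to characterise vulnerability in patients aged 85 years or older. A mortality figure from consenters, shown without its condition, is likely to be taken as the mortality of such patients after admission through the ED. The handling named in the article deals with losses after entry, such as the expected dropout at six weeks. Low power is a matter of precision and neither discloses nor corrects selection at entry.

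**Working it through.** **1. The plan's own figure.** 281 × 0.50 = 140.5, against about 139 stated; 139/281 = 49.5%. The figure reproduces to the rounding of its inputs. About 281 − 139 = 142 eligible patients would stay outside the cohort.

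**2. Mortality, by the share of decedents who had consented.** Let m be true in-hospital mortality among the 281 eligible, and c the share of those who die in hospital who had consented before death. With 139 enrolled,

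observed mortality = 281 × m × c / 139.

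The documents give neither m nor c; both are assumptions. For m = 10%:

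| c | Deaths among participants (281 × 0.10 × c) | Observed mortality |
|---|---|---|
| 10% | 2.8 | 2.0% |
| 20% | 5.6 | 4.0% |
| 30% | 8.4 | 6.1% |
| 40% | 11.2 | 8.1% |
| 45% | 12.6 | 9.1% |
| 49.5% | 13.9 | 10.0% (no bias) |

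Over c = 10% to 45%, m = 5% gives 1.0% to 4.5% and m = 15% gives 3.0% to 13.6%. Mortality is understated whenever decedents had consented less often than the overall 49.5%.

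**3. Mortality, separating the two mechanisms.** Let f be the share of in-hospital deaths that occur before consent, and r the consent probability of later decedents relative to survivors. Then

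observed mortality = m(1 − f)r / [m(1 − f)r + (1 − m)].

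For an assumed m = 5% (7.0 deaths expected in 139 unselected patients):

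| f | r | Observed mortality | Deaths in 139 |
|---|---|---|---|
| 0 | 1 | 5.0% | 7.0 |
| 10% | 1 | 4.5% | 6.3 |
| 30% | 1 | 3.6% | 4.9 |
| 30% | 0.5 | 1.8% | 2.5 |
| 50% | 0.5 | 1.3% | 1.8 |

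With r no greater than 1, the observed value never exceeds the true one, and equals it only if no death precedes consent (f = 0) and later decedents consent as readily as survivors (r = 1).

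**4. Length of stay.** As an illustration, assume a gamma distribution (shape 3) with mean 14 days. Restricting it to stays longer than 3, 5 or 7 days raises the mean to 14.3, 15.1 or 16.2 days. The shift is upward, and small if consent comes early.

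**5. The heat-mortality association.** Let the enrolment probabilities of decedents and survivors be D1 and S1 on heat days, and D0 and S0 on other days. Then

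observed odds ratio = true odds ratio × (D1/S1) / (D0/S0).

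If decedents are under-enrolled by the same factor on both kinds of day, D1/S1 = D0/S0 and the odds ratio is unchanged, although absolute mortality is still too low. If the two ratios differ, the odds ratio moves down or up according to which is larger, and nothing in the article settles that. This result is for the mortality odds ratio; I have not worked out an equivalent for mean length of stay.

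**The case against.** **The analysis is deferred.** The article refers detailed substudy procedures to the registry record and the substudy protocol, which are not at hand, and time origin or delayed entry could be set there. That would count against a complaint of missing detail. Here, however, the entry rule and the outcomes are both stated in the article, and no further detail lets a patient who died before consent be enrolled under that rule. The article also does not say that the unseen documents handle this.

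**The estimand is not stated.** The article nowhere claims to estimate mortality of all oldest-old ED admissions. Mortality among participants is a valid descriptive quantity. This stands, and it is why a conditional interpretation is enough. It also matters that the geriatric cohort is read here as the consented participants; if routine data on all screened patients were used on another legal basis, the problem would not arise, but the article does not say so.

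**Recruitment measures.** Dedicated ward staff, repeated opportunities to inform patients and contact with legal representatives could shorten the time to consent and bring in some sicker patients. A reader might infer that only patients well enough to sign can enter; that is partly inference. The measures narrow the gap but cannot recover a death or discharge before the approach.

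**Two stronger readings should be resisted.** One is that any heat-mortality association must be pulled towards no effect. Step 5 shows that this needs selection differing by exposure in one particular direction. The other is that mortality will be understated several-fold. That follows only from assuming that few decedents had consented; the documents give no such share, and values just below 49.5% produce a mild bias.

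**Conclusion.** The point holds as a structural mismatch between the entry rule and two secondary descriptive outcomes of an exploratory substudy. Relative to all eligible geriatric admissions, mortality will tend to be too low and length of stay too high. For mortality, the direction rests on some deaths preceding consent, or later decedents consenting less often than survivors. For length of stay, it rests on some stays ending before consent.

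The size is unknown. It ranges from negligible to a several-fold understatement of mortality, depending on assumed quantities that the documents do not supply. No claim can be made about the direction of any distortion of a heat-outcome association. The primary analysis (O1) and the registry-based secondary objectives are untouched. Importance is minor to moderate.

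**What to change.** 1. Record the date of consent for each participant.
2. Analyse in-hospital mortality and length of stay with delayed entry, so that a patient contributes from consent onward.
3. Report the distribution of days from admission to consent.
4. State with the results that both figures are conditional on enrolment and do not estimate mortality or length of stay from admission for all eligible patients. This is needed alongside delayed entry, which handles the time before consent but does not remove any tendency of fitter patients to consent.
5. If possible, add an unselected comparison from the registry: the same age group admitted via the ED. This depends on what the registry holds. Routine ED Records lists the ED disposition and, from the inpatient billing data, names only the discharge diagnosis. The descriptive analysis section mentions "hospital stay duration, discharge outcomes" without saying whether in-hospital death after admission is included. Availability must be confirmed, and the different period (2019-2024) and the wider population, not limited to geriatric wards, noted.

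Removing the two outcomes is not necessary and would lose their link to the functional and questionnaire data. The cost is one extra recorded date, some wording, and slightly less precise estimates because time before consent is not counted. The registry comparison, if feasible, is one further tabulation.
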